### Qualitative interviews

Interviews/Yarns with community and health professionals will be completed before and after the intervention from all six sites participating in the RCT. Qualitative evaluation will be conducted using Yarning methodology [5]. Yarning is considered “a way to safely engage with participants to explore research questions relating to the topic of the study” [25].

We anticipate the recruitment of 60 participants in the qualitative aspect of the study to achieve saturation of findings (ten per site – 5 community members and 5 stakeholders).

Yarns would be conducted prior to the intervention (RCT) and after 6–12 months of the intervention period, in order to identify barriers and facilitators for breastfeeding, and to assess acceptability of the new peer support breastfeeding intervention.

#### Sites

Participants for yarns/interviews will be recruited from the six sites participating in the RCT.

#### Sample size

60–66 participants to reach saturation of findings.

#### Recruitment

Members of the operation team will liaise with site staff in regarding the recruitment of community members (aged over 14 years, and if under 18, parental written or verbal consent required) and stakeholder/staffs (aged over 18) working within the service.

#### Consent

Community participants would be given a participant information sheet (PIS) and service providers would be given a separate PIS. Written consent will be required. All information would be also delivered verbally by the research team. Community participants would be asked for written consent (or recorded verbal consent where this was impossible). Service providers would be asked for written consent (or recorded verbal consent where this was not possible). All participants will be given a study ID to de-identify personal information in transcription and analysis. We will collect basic demographic details from participants (age, gender, role or relationship to participant).

Yarns will be conducted with the following:

##### Community members

participants, partners and aunties/grannies (10–15 before intervention and 10–15 after peer worker in place).

##### Health professionals

we plan to Yarn with AHWs, Aboriginal Health Practitioners, child health nurses and midwives, general practitioners, ABA volunteers and lactation consultants. (10–15 before intervention and 10–15 after peer worker is in place) as well as interviews with the six peer workers.

#### Data Collection

Yarns will be conducted either face to face as an interview or focus group, which will be digitally audio-recorded or using online video/phone interview where face to face interaction is not possible (also audio-recorded). These would be transcribed by an Australian transcription service. Interviews/ focus groups would be conducted using a Yarning guide. Community participants will be offered a $50 voucher for participating in the interview or focus group.

#### Analysis

Transcriptions will be analysed, using Yarning methodologies [5] and grounded theory to develop themes of barriers and facilitators to breastfeeding with and without access to a peer worker. We also plan to use the theory of planned behaviour [26] to consider factors contributing to breastfeeding choices and interaction with peer support worker [27].

### Video Development

This project also involves development of educational videos to support breastfeeding. We plan to evaluate these resources once developed through small focus groups or interviews (when shown in a group) using Yarning methodology. Yarns will be conducted either in face to face as an interview or focus group (from an interview guide), which will be digitally audio - recorded or using online video intervention where face to face interaction is not possible (also audio-recorded). These would be transcribed by an Australian transcription service.

#### Recruitment

We plan to recruit community members (10–15) and service providers (10–15) to evaluate the videos.

#### Consent

Community participants will be given a PIS and service providers would be given a separate PIS. Written consent will be required. All information would be also delivered verbally by the research team. Community participants would be asked for written consent (or recorded verbal consent where this was not possible). Service providers would be asked for written consent (or recorded verbal consent where this was not possible). Community participants will be offered a $50 voucher for their participation. All participants will be given a study ID to de-identify personal information in transcription and analysis. We will collect basic demographic details from participants (age, gender, role or relationship to participant).

#### Sample size

10–15 community members and 10–15 service providers which was chosen so as to reach saturation of findings.

#### Interviews

Interviews/ focus groups will be conducted using a Yarning guide.

#### Analysis

We plan to use an inductive thematic analysis to consider views on the resources developed.

### Data Management

#### Confidentiality, Privacy and Data Integrity

The consent process will ensure that data collected about participants is stored to preserve confidentiality according to legal standards. Data will be collected onto an online secure database, REDCap*©* via a laptop computer, backed up daily. Audio and transcribed files will also be stored digitally, backed up daily on Cloudstor. All data would be de-identified prior to analysis, and publication.

A subgroup of investigators will form the Data Monitoring Committee which will meet annually to review data security and quality and accuracy of data collection.

#### Study records retention

All electronic data will be stored for 15 years following completion of the project, on the password locked University of Wollongong secure server (Research Data Storage and Management system, Cloudstor).

#### Data Handling and Management Responsibilities

Data will be stored securely in a password locked secure server (Cloudstor) at University of Wollongong. The ACCHS and AMIHS maternal and child health agencies involved will be given access to their site data and will be given feedback about the results of the project and asked for permission for public release, for example of reports, journal articles or conference presentations.

#### Trial governance

The project will appoint an Aboriginal Steering Committee, including investigators, midwife/ves, AHWs and consumers who will meet biannually. The purpose of the steering committee will be to advise the research team about appropriate service delivery models.

A subgroup of investigators will form the Data Monitoring Committee which will meet annually to review data security and quality and accuracy of data collection.

#### Dissemination of results

Our research team’s previous research work has focused on work that is developed and driven by the community and prioritises feedback to the community in addition to research outputs in the form of journal articles and conference presentations. Results would be offered (in the form of a culturally appropriate email summary) to all participants and will be fed back to community boards/managers verbally, in an easy-to-read report and infographic. Reporting would include specific recommendations on evidence for the economic benefits of this intervention. Findings will also be fed back to ACCHSs, state health services and the ABA where findings recommended changes to service delivery, for example evidence of effectiveness breastfeeding peer support workers.

### Health Economics

Health economic analysis will include assessment of incremental study and health system cost per additional breastfeeding woman, as assessed in the FEST study and more generally joint incremental effects and costs estimated under uncertainty [21]. Costs estimated will include direct costs of intervention staff time and overheads, their training with the Australian Breastfeeding Association, cost of car use in accessing populations, program consumables and $50 voucher for intervention participants completing 4 months follow up as observed in study and modelled downstream health system costs associated with effects of breastfeeding in each arm observed on study.

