#### Sample size

We plan to recruit a total of 720 participants (120 at each site), allowing for a predicted 15% drop out at 6 months post-birth, resulting in 612 participants for analyses.

A similar intervention, the RUBY Study (Forster et al., 2017) was able to follow-up 88% of participants so we believe a 15% drop-out rate is likely conservative.

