#### Participant recruitment

Recruitment of participants will be conducted from 28 weeks gestation and survey collection will occur from 32 weeks gestation with care to recruit young and marginalised women to prevent under-sampling.

Staff at the participating sites will offer the woman a show bag containing information about the project, giveaways (as determined by staff at the site, funded by the project), and the Participant Information Statement PIS). Staff will ask verbal permission from the participant to pass on their mobile phone number (landline and/or email) to the research team so they may to be contacted regarding the study.

Staff at the sites will record the potential participant’s name on a log that contains the woman’s name, mobile number, and Estimated Due Date (EDD). This information will be scanned by the staff member and emailed or faxed to the research team, weekly.

All participants will be provided with a $50 gift card at the six-week interview (6 weeks post-birth) as an incentive for participating in the project. Those who do not have a mobile phone can be provided with one as part of the project.

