#### Data collection

A research assistant or associate research fellow will collect data. The research team will call potential participants that have provided their contact details. They will again be verbally given information about the project, from the PIS and will be asked to provide verbal consent. Surveys will be collected at these time-points (see Fig. 2):

Baseline (32–40 weeks of gestation).6 weeks post-birth (after which a $50 voucher will be sent to participant).4 months post-birth.6 months post-birth.12 months post-birth (SMS message).

If participants are not contactable by telephone after three attempts, a link to the survey will be emailed to them or sent via SMS (to a maximum of three times over three weeks). Permission will also be requested for the maternal and child health team to inform peer workers when the women have given birth to their babies, in order to ensure early access to the intervention.

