#### Analysis

Data from telephone/email surveys at baseline prior to birth, 6 weeks, 4 months and 6 months will be entered into a matrix in REDCap ©, an electronic data collection program by the research team. This data will be collated into Excel, cleaned and analysed, with supervision by the biostatistician. Data will be coded, Statistician and Health Economist will remain blinded throughout the length of the study.

Peer worker interactions with participants will be logged, along with notes about factors which might affect uptake (i.e. participants not available to respond, other priorities such as funerals) so as to undertake process analysis, in addition to outcome analysis. This will be scanned/emailed to the research team for analysis.Interactions with participants will be logged by peer workers (on paper/electronic, stored in a locked secure environment at the site, then emailed or scanned to the research team and entered into REDCap©) to ensure scheduled visits had occurred, and to record any issues that could be incorporated into a process analysis (e.g. participant did not respond, participant had moved).We will use ‘journal’ reflective practice data for analysis of Aboriginal peer workers’ interactions [24].

We plan to recruit at least 360 participants and 306 participants completing 6 weeks in both of group 1 (intervention) and group 2 (control), with three sites in each group (120 participants and 102 completing 6 weeks per site assuming 15% drop out) providing 80.1% power to detect a difference between the group proportions of 0.1500. The proportion in group 1 (the treatment group) is assumed to be 0.2500 under the null hypothesis and 0.4000 under the alternative hypothesis. The proportion in group 2 (the control group) is 0.2500. The test statistic used is the two-sided Z-Test (Pooled), the intra-cluster correlation is 0.0100 and the significance level of the test is 0.050.

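### The economic analysis costs a $50 voucher for the intervention arm at 4 months, but the trial procedures give it to all participants at six weeks; the sections need reconciling

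*Protocol article*

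**What the plan says.** Three places in the protocol article describe a $50 payment to trial participants.

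- **Participant recruitment:** "All participants will be provided with a $50 gift card at the six-week interview". The payment is described as an incentive for taking part.
- **Data collection:** the survey schedule attaches the payment to one time point, "6 weeks post-birth (after which a $50 voucher will be sent to participant". Nothing is listed against the 4-month, 6-month or 12-month contacts, and no distinction is made by arm.
- **Health Economics:** the measure is an "assessment of incremental study and health system cost per additional breastfeeding woman". The list of costs includes, in dollars, a "50 voucher for intervention participants completing 4 months follow up as observed in study". No voucher is listed for control participants.

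The other $50 vouchers in the article are for community members who take part in the qualitative yarns or the video evaluation. They belong to other parts of the study and do not explain the difference.

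**The concern.** The first two sections are consistent with each other. The third differs from them on who is paid (intervention participants, not all) and on when (4 months, not six weeks). Each way of resolving the difference has a consequence.

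**Reading A: one voucher, all women, six weeks.** A payment made equally in both arms cancels in an incremental cost. Charged to the intervention arm only, it enters in full and makes peer support look dearer than it is. The article says its reporting will include specific recommendations on the economic benefits of the intervention, so the incremental cost matters to how the results are used.

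**Reading B: a further voucher, intervention arm only, at 4 months.** The cost is then real, but one arm is rewarded for completing the follow-up at which a primary outcome, exclusive breastfeeding at 4 months, is collected by self-report. Response could then depend on arm.

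**Working it through.** **Inputs**

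- Voucher value: $50 (all three sections).
- Enrolled and completing per arm: 360 and 306, from "We plan to recruit at least 360 participants and 306 participants completing 6 weeks in both of group 1 (intervention) and group 2 (control" (RCT Analysis section).
- Cluster structure: "three sites in each group (120 participants and 102 completing 6 weeks per site assuming 15% drop out" (same section).
- Planned risk difference in exclusive breastfeeding at six weeks: 0.40 − 0.25 = 0.15; ICC 0.01; two-sided 5% level (same section).
- The Sample size section places the same 15% loss at six months: "allowing for a predicted 15% drop out at 6 months post-birth". Using 306 as the number completing 4 months is therefore an assumption that fits either statement. The ceiling is 360.

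**Check on the inputs.** The plan gives no voucher total or cost ratio to reproduce. Its stated power of 80.1% uses the same 306 and 0.15, and it does reproduce:

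- Design effect = 1 + (102 − 1) × 0.01 = 2.01; effective size per arm = 306 / 2.01 = 152.24.
- Standard error under the null (pooled proportion 0.325) = √(2 × 0.325 × 0.675 / 152.24) = 0.0537; under the alternative = √((0.25 × 0.75 + 0.40 × 0.60) / 152.24) = 0.0530.
- Power = Φ((0.15 − 1.96 × 0.0537) / 0.0530) = 0.801.

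The voucher plays no part in this power figure.

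**Reading A: paid to all at six weeks**

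| Quantity | Charged to both arms | Charged to intervention arm only |
|---|---|---|
| Intervention-arm voucher cost | 306 × $50 = $15,300 | $15,300 |
| Control-arm voucher cost | 306 × $50 = $15,300 | $0 |
| Incremental voucher cost | $0 at equal retention | $15,300 |

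If all 360 complete, the overstatement is 360 × $50 = $18,000.

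Effect on cost per additional exclusively breastfeeding woman:

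- Per completer: $15,300 / (0.15 × 306) = $15,300 / 45.9 = $333.
- Per enrolled woman, with 0.15 applied to all enrolled: ($50 × 0.85) / 0.15 = $42.50 / 0.15 = $283.

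If retention differs between arms, the true increment is not exactly zero, but it is small. For an assumed difference of 3 to 10 points it is $50 × 0.03 = $1.50 to $50 × 0.10 = $5.00 per enrolled woman.

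**Scale against the trial's own costs.** The Intervention section employs peer workers three days a week for three years in three communities. With one worker per community that is 0.6 × 3 × 3 = 5.4 full-time years. The article gives no wage. Assuming $60,000 to $100,000 per full-time year, staffing is $324,000 to $540,000, and $15,300 is 4.7% to 2.8% of it. Overheads, training, car use and consumables, or more than one worker per site, would lower that share.

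**Reading B: a further intervention-only voucher at 4 months.** The $15,300 (up to $18,000) is then a genuine incremental cost. What changes is the follow-up: women in both arms receive $50 at six weeks, and intervention women alone receive another $50 for completing 4 months. The article gives no response rate by arm and no estimate of how an incentive affects response, so no size can be attached.

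**The case against.** The strongest defence is that the Health Economics line is loose drafting in a condensed article. Its list of costs is not presented as exhaustive, it never says that control-arm vouchers go uncosted, and it ties costs to what is observed in the study. An analysis built on actual payments would record vouchers in both arms, and no bias would follow. This is fair as far as it goes, so bias is conditional on the line being applied as written. It does not remove the point, because the one voucher the line names is restricted to one arm and placed at a different time from the incentive described elsewhere.

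Three stronger readings are tempting, and the documents do not support them.

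- *The voucher could dominate the cost-effectiveness ratio.* A reader might set $333 beside the £91 per additional exclusively breastfeeding woman quoted in the Background from a Scottish telephone-support trial. Those figures are in different currencies and concern a different intervention. Against this trial's own staffing the voucher is a few percent.
- *The sections are logically incompatible.* They are not: a six-week voucher for all does not exclude a second one at 4 months. They are unreconciled.
- *Follow-up is biased at two of the three primary time points.* Reading B gives a risk, not a demonstrated bias. It is direct at 4 months and at most indirect at 6 months, because the voucher does not reward the 6-month survey.

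Two further objections stand. The 0.15 difference is a six-week effect, so the $283 to $333 range shows scale at that time point and is not a 4-month estimate. And since the stated measure includes study costs, leaving the voucher out altogether is not required; charging both arms is enough.

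**Conclusion.** The inconsistency is real, and nothing else in the article resolves it. Under Reading A, applying the costing line as written overstates incremental cost by $50 per intervention completer: about $15,300 in total, or $283 to $333 per additional exclusively breastfeeding woman. This assumes 306 intervention completers, the planned 0.15 difference at six weeks, and no voucher charged to controls. The direction is fixed, against the intervention; the size is modest, with the comparison to staffing resting on assumed wages. Under Reading B the cost is correct, but the follow-up incentive differs by arm at the 4-month primary time point, with an effect that cannot be quantified from the article. The documents do not show which reading reflects practice. The point should be corrected before the economic analysis is run. Under Reading A it does not touch the primary effectiveness analysis.

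**What to change.** Reconcile the Participant recruitment, Data collection and Health Economics sections so that they state the same recipients, the same timing and the same costing rule.

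- **If the voucher is paid to all participants:** correct the Health Economics line. Then either cost the voucher identically in both arms, which nets to about zero, or exclude it from both as a research cost. This is a one-line change and needs no new data.
- **If a voucher is paid to the intervention arm only:** either offer the same follow-up incentive in both arms, at about 306 × $50 = $15,300 for the control arm (at most $18,000), or disclose the difference in the recruitment and data collection text and report 4-month and 6-month response by arm. Disclosure and reporting need only data already being collected.

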## Discussion

This study will be an opportunity to explore the peer support approach to promote initiation and continuation of breastfeeding in Aboriginal and Torres Strait Islanders. Potential outcomes could be trialling a new workforce model to include community roles within the health service.

## Data Availability

The data will not be part of a public repository but datasets may be accessed at completion of study pending ethics approval.
